#### DCC+MISA group

From Aug. 31, 2025 to Oct. 31, 2027. Infants without contraindications to DCC, as determined by prenatal evaluation, receive immediate non-invasive respiratory support after birth. DCC is successfully performed for 60 s, followed by a diagnosis of NRDS. A therapeutic dose of PS is administered via MISA within the first 2 h after birth.

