#### ICC+tracheal intubation group

From Jan.1, 2017 to Dec. 31, 2020. Umbilical cord clamping occurs within 20 s after birth. Infants are diagnosed with NRDS and receive a therapeutic dose of PS via tracheal intubation within the first 12 h after birth.

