#### ICC+MISA group

From Jan.1, 2021 to Dec. 31, 2024.Umbilical cord clamping is performed within 20 s after birth. Infants are diagnosed with NRDS and receive a therapeutic dose of PS via MISA within the first 2 h after birth.

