### Quality control

This trial adheres to Good Clinical Practice (GCP) standards and meets the requirements set by the Ethics Committees. It is conducted under the supervision of the Ethics Committees at the participating institutions. A Data Safety Monitoring Board (DSMB) will be established, comprising two independent neonatologists and an independent statistician. The DSMB will have designated review points to assess trial progress and safety.

In clinical practice, neonatologists receive training on MISA and DCC before rotating to the NICU, and undergo regular assessments. This ensures that there are neonatologists proficient in MISA and DCC on duty 24 h a day, who can perform the corresponding clinical procedures for preterm infants delivered at any time. Upon entering the NICU, nasal continuous positive airway pressure (NCPAP) or nasal intermittent positive pressure ventilation (NIPPV) will be initiated as the first line of non-invasive respiratory support. During MISA, the infant is placed in an incubator with the temperature set at 37°C. The infant's limbs are properly swaddled to soothe them, preventing crying and injury. A laryngoscope is used to expose the glottis, and a thin catheter is inserted under the maintenance of non-invasive ventilation support, with the insertion depth calculated as (infant's weight in kg) + 5.5/6 cm. Pulmonary surfactant (Curosurf, 200 mg/kg or Calf Pulmonary Surfactant for Injection, 100 mg/kg) is slowly instilled, with the total administration time being approximately 3 min. If the infant cries or experiences a drop in heart rate or oxygen saturation, the administration is paused; it is resumed after the infant's condition stabilizes until the full dose is administered.

In collaboration with the obstetrics department, operational protocols for DCC during deliveries in the labor room and operating room have been developed. Monthly training on neonatal resuscitation for asphyxia and DCC is provided to midwives and obstetricians, ensuring that the condition of newborns is quickly evaluated during delivery and that safe DCC is performed for those without contraindications.

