DCC not only enhances the transfer of blood from the placenta to the fetus, improving hemoglobin reserves in premature infants, but it also stabilizes the establishment of pulmonary circulation in the early postnatal period. Since placental circulation provides 30%–50% of cardiac blood flow, immediate clamping of the umbilical cord can lead to a significant drop in venous return and cardiac output. DCC facilitates a smoother transition until premature infants can establish effective pulmonary ventilation and circulation. Thus, DCC serves as a crucial component of early respiratory and circulatory management for these infants. This study aims to determine whether the simultaneous application of DCC and MISA further enhances survival and prognosis in premature infants. Given our recent implementation of DCC for infants born before 30 weeks, we designed a NICU quality improvement study to evaluate the efficacy of DCC combined with MISA by comparing prospective and retrospective cohorts.

Despite the potential of this study, there are some limitations to consider. As a quality improvement study, data for the ICC and MISA and ICC and tracheal intubation groups were collected retrospectively, which may introduce biases due to variations in hospitalization years and treatment approaches. Furthermore, the retrospectively collected data are based on the diagnosis, treatment, and evaluation conducted by clinicians, and there may be variations in this process. To minimize these discrepancies, we limited the study to preterm infants from the past six years for the retrospective cohort. Additionally, both the prospective and retrospective cohorts adhered to the same inclusion and exclusion criteria to reduce intergroup differences and enhance the validity of the conclusions.

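### Immediate non-invasive support at birth is a condition of the DCC+MISA group only, so its contrast with ICC+MISA may mix cord management with delivery-room support

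*Protocol article*

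**What the plan says.** Under Research grouping, the DCC+MISA definition reads: "Infants without contraindications to DCC, as determined by prenatal evaluation, receive immediate non-invasive respiratory support after birth". It continues: "DCC is successfully performed for 60 s, followed by a diagnosis of NRDS", with surfactant by MISA within 2 h.

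The ICC+MISA definition has two treatment elements: "Umbilical cord clamping is performed within 20 s after birth" and "Infants are diagnosed with NRDS and receive a therapeutic dose of PS via MISA within the first 2 h after birth". The ICC+tracheal intubation definition has the same clamping limit, and its infants "receive a therapeutic dose of PS via tracheal intubation within the first 12 h after birth". Neither ICC definition mentions respiratory support at birth.

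The Quality control section, without limiting the statement to a group, says: "Upon entering the NICU, nasal continuous positive airway pressure (NCPAP) or nasal intermittent positive pressure ventilation (NIPPV) will be initiated". It also describes MISA as carried out while non-invasive support continues.

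The variables listed under Data collection and diagnoses include duration of NCPAP/NIPPV, but not whether or when support began in the delivery room. Under Statistical analysis, the adjusted model for BPD takes in baseline variables that differ between groups at P < 0.1.

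The Discussion states the aim: "This study aims to determine whether the simultaneous application of DCC and MISA further enhances survival and prognosis in premature infants".

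**The concern.** DCC+MISA and ICC+MISA share the surfactant method and the 2 h window. By design their contrast is the one that could show what a change in cord management adds. A second treatment element, support begun at birth, is written into one side of that contrast only.

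The element matters for the primary outcome by the article's own reasoning: the Background treats respiratory and circulatory stability after birth, together with little early invasive ventilation, as essential to preventing BPD. Support at birth also acts in the same minutes in which, according to the Discussion, DCC eases the transition to breathing.

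If fewer ICC+MISA infants had such support, part of any fall in BPD would belong to it, and the listed variables and the adjustment rule would not reveal this. A variable that is not abstracted cannot pass a P < 0.1 screen.

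**Working it through.** **1. The definitions side by side (Research grouping)**

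| Element | ICC+tracheal intubation | ICC+MISA | DCC+MISA |
|---|---|---|---|
| Cord clamping | within 20 s | within 20 s | DCC for 60 s |
| Support at birth | not stated | not stated | immediate, non-invasive |
| Surfactant route | tracheal tube | MISA | MISA |
| Surfactant window | 12 h | 2 h | 2 h |

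Between the last two columns, two rows differ as written: clamping and support at birth. The intubation group also differs from DCC+MISA in route and window, so that contrast could not isolate DCC in any case.

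**2. What other sections settle**

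- Inclusion and exclusion criteria: every infant breathes spontaneously and was not intubated before surfactant. This says nothing about whether or when non-invasive support began.
- Quality control, and the definition of MISA success under Quality improvement-related indicators: MISA takes place under non-invasive support. Both MISA groups therefore had support by the time of surfactant, at most 2 h after birth.
- Quality control: first-line NCPAP/NIPPV starts at NICU entry. Any undocumented difference between the MISA groups is thus confined to the interval from birth to NICU entry.

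**3. The planned effect that this contrast must carry**

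Inputs from Sample size calculation: p1 = 0.29, p2 = 0.14, k = 3, z-values 1.96 and 0.84.

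n2 = (1.96 + 0.84)² × [0.29 × 0.71/3 + 0.14 × 0.86] / 0.15² = 7.84 × 0.18903 / 0.0225 = 65.87, so 66, and n1 = 3 × 66 = 198. With 10% loss, 66/0.9 = 73.3, so 74, and 3 × 74 = 222. The plan's figures reproduce. The planned effect is 15 points.

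**4. How much of it support could account for (assumptions only)**

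The article gives neither the effect of support at birth on BPD nor the share s of ICC+MISA infants who had it. With an assumed effect d, and support in every DCC+MISA infant by definition:

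part due to support = d × (1 − s)

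| Assumed d | s = 30% | s = 70% | s = 100% |
|---|---|---|---|
| 5 points | 3.5 | 1.5 | 0 |
| 10 points | 7 | 3 | 0 |

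**5. Consequence for the test (illustration)**

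Suppose DCC has no effect, ICC+MISA has 29% BPD, and a net difference D = d × (1 − s) comes from support alone. With 66 versus 198 infants,

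SE = √[(0.29 − D)(0.71 + D)/66 + 0.29 × 0.71/198]

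and the chance of a two-sided P < 0.05 is Φ(D/SE − 1.96) + Φ(−D/SE − 1.96).

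| Net difference D | 0 | 2 | 5 | 7 | 8 | 10 points |
|---|---|---|---|---|---|---|
| Chance of significance | 5% | 6% | 13% | 21% | 27% | 41% |

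For D = 7 points: SE = √(0.22 × 0.78/66 + 0.2059/198) = 0.0603, D/SE = 1.16, and the chance is 0.21. A net D of 10 points would need d = 10 with no control supported, or a larger d. This uses the unpooled normal approximation of the plan's formula; a χ² test with continuity correction would give somewhat lower chances.

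**The case against.** The case on the other side is substantial, and most of it stands.

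- **Silence is not absence.** The ICC definitions are short labels in a journal article. Nothing says that ICC infants went without support at birth, and spontaneously breathing infants under 30 weeks may well have had it. This stands, and it is why the possible bias starts at zero.
- **The gap is narrow.** MISA is done under non-invasive support within 2 h in both MISA groups. This stands: only the time before NICU entry is in question.
- **The sections need not conflict.** Support at birth followed by NCPAP/NIPPV on NICU entry is a plausible sequence. This stands; the point is an omission for the ICC groups and not a contradiction.
- **The aim is the combination.** The Discussion, the Conclusion and the planned adjusted odds ratio all concern DCC plus MISA, and support could be read as part of how DCC is delivered. This stands in part. The name of the regimen, the aims and the conclusion do not include immediate support, and a difference from ICC+MISA will naturally be read as the gain from DCC.
- **The limitations already concede bias** from calendar years and treatment approaches. True in general terms, but the remedies given there (shared eligibility criteria and a limited retrospective period) do not deal with this element.

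A reader might infer that no BPD difference could be attributed to DCC at all. The article does not support that: the imbalance is unquantified and may not exist.

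**Conclusion.** The point holds in a limited form. Support at birth is a condition of the DCC+MISA group only, its use in the ICC groups is not stated, and the listed variables and the adjustment rule would not bring it into the comparison that drives the sample size. That comparison may therefore mix cord management with a difference in support between birth and NICU entry.

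The size is unknown. It is zero if support at birth was routine in all periods. Under the assumed 5 to 10 point effect and a 30% to 100% share among controls, it is 0 to 7 points of the planned 15. Neither range comes from the article. The finding calls for recording one more element and for care in attribution; it does not invalidate the comparison.

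**What to change.** 1. Abstract from the birth record, in all three groups, whether non-invasive support was started in the delivery room and when. Report both by group. State in the ICC definitions what is known about support at birth in those periods.
2. Add a sensitivity analysis of DCC+MISA versus ICC+MISA that is restricted to infants with delivery-room support, or adjusts for it whatever its baseline P value. Restriction is the cleaner choice: since every DCC+MISA infant has support by definition, an adjusted model can learn the effect of support only from ICC infants.
3. If the historical records do not hold the information, or no ICC+MISA infant had support, neither analysis is possible. Then describe the intervention and the conclusion as DCC with immediate non-invasive support plus MISA, and do not attribute a difference from ICC+MISA to DCC alone.

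Cost: one or two more fields from existing records, a narrower claim if they are missing, and possibly fewer controls in the sensitivity analysis. With shares of 30% and 70%, for example, restriction would leave about 67 (0.3 × 222) and 155 (0.7 × 222) of the 222 ICC+MISA infants. The main analysis and the sample size stay as planned.

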### Participants

All infants participating in the study were selected using the same inclusion and exclusion criteria.

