#### Inclusion criteria

① Infants of 23–29 + 6 weeks gestational age.② Born in Peking University Third Hospital, having spontaneous breathing after birth;③ Diagnosed as NRDS; NRDS is defined as progressive dyspnea that occurs after birth, with or without imaging evidence, excluding other causes of dyspnea.

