#### Quality improvement-related indicators

The rate of first-time pulmonary surfactant administration via MISA among all preterm infants with a gestational age of 23–29 + 6 weeks admitted to the NICU and the trend of this rate changing over years.The success rate of MISA (defined as the completion of pulmonary surfactant administration under non-invasive support, without early termination of administration or switching to tracheal intubation for administration).The rate of DCC among all preterm infants with a gestational age of 23–29 + 6 weeks admitted to the NICU and the trend of this rate changing over years.

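### Entry to the DCC+MISA group requires DCC eligibility and a completed 60 s of DCC; the ICC groups have no matching screen, which could bias the comparison towards DCC+MISA

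*Protocol article*

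**What the plan says.** Under Research grouping, the DCC+MISA group (31 August 2025 to 31 October 2027) has two entry conditions concerning the cord. One is prenatal: "Infants without contraindications to DCC, as determined by prenatal evaluation". The other is met only after birth: "DCC is successfully performed for 60 s, followed by a diagnosis of NRDS".

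The ICC groups carry one cord condition each. For ICC+tracheal intubation (2017-2020): "Umbilical cord clamping occurs within 20 s after birth". For ICC+MISA (2021-2024): "Umbilical cord clamping is performed within 20 s after birth". Neither mentions eligibility for DCC.

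The Participants section states: "All infants participating in the study were selected using the same inclusion and exclusion criteria". The limitations paragraph of the Discussion relies on this as a way to make the groups more alike and the conclusions sounder. The biases that paragraph names are calendar years, treatment approaches and variation between clinicians. Selection by DCC eligibility or completion is not among them.

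**The concern.** The prospective group is defined by treatment successfully received, and only among infants judged suitable for it. The historical groups are defined by a practice that was routine in their period and applied without regard to suitability for DCC. An infant born in 2026 with a prenatal contraindication, or whose cord was clamped before 60 s, enters no group: the DCC+MISA definition shuts it out, and both ICC groups closed at the end of 2024. A comparable infant born in 2017-2024 and clamped within 20 s can be a control, provided it meets the common criteria.

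If the infants filtered out have a higher risk of BPD or death than the rest, the DCC+MISA group would look better than its controls even with no effect of DCC. The comparison with ICC+MISA is the one the sample size was calculated for, so the study's main conclusion is exposed.

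**Working it through.** **1. Group entry side by side**

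| Condition | ICC+intubation | ICC+MISA | DCC+MISA |
|---|---|---|---|
| Listed inclusion/exclusion criteria | yes | yes | yes |
| No prenatal DCC contraindication | not screened | not screened | required |
| Cord condition | within 20 s | within 20 s | 60 s completed |
| NRDS | required | required | required |
| Surfactant | intubation, within 12 h | MISA, within 2 h | MISA, within 2 h |

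The statement about common criteria is accurate for the first row. It does not cover the second row, nor the success condition in the third. Between ICC+MISA and DCC+MISA, the NRDS and surfactant conditions are the same.

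**2. The plan's own figure**

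Inputs from Sample size calculation: p1 = 0.29, p2 = 0.14, k = 3, z values 1.96 and 0.84.

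n2 = (1.96 + 0.84)² × [0.29 × 0.71 / 3 + 0.14 × 0.86] / 0.15² = 7.84 × 0.18903 / 0.0225 = 65.87, so 66, and n1 = 3 × 66 = 198. After 10% loss: 66 / 0.9 = 73.3, so 74, and 3 × 74 = 222. The stated sizes reproduce. They serve here only as a yardstick: the design effect is 15 points.

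**3. How large the selection effect might be**

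The documents give neither the share filtered out nor its BPD risk. Assume:
- q = share of otherwise eligible infants who are contraindicated or do not complete 60 s: 10-40%;
- RR = their BPD risk relative to the others: 1.5-2;
- overall risk without DCC: 29%, the plan's ICC+MISA figure;
- no true effect of DCC.

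With a the risk among retained infants, 0.29 = (1 − q)a + q·RR·a, so a = 0.29 / [(1 − q) + q·RR].

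| q | RR | a | Spurious fall (points) | Share of 15 points | Chance of a significant result favouring DCC+MISA |
|---|---|---|---|---|---|
| 0.1 | 1.5 | 0.29/1.05 = 0.276 | 1.4 | 9% | 3.9% |
| 0.1 | 2 | 0.29/1.10 = 0.264 | 2.6 | 18% | 5.8% |
| 0.2 | 1.5 | 0.29/1.10 = 0.264 | 2.6 | 18% | 5.8% |
| 0.2 | 2 | 0.29/1.20 = 0.242 | 4.8 | 32% | 10.8% |
| 0.3 | 1.5 | 0.29/1.15 = 0.252 | 3.8 | 25% | 8.1% |
| 0.3 | 2 | 0.29/1.30 = 0.223 | 6.7 | 45% | 17.2% |
| 0.4 | 1.5 | 0.29/1.20 = 0.242 | 4.8 | 32% | 10.8% |
| 0.4 | 2 | 0.29/1.40 = 0.207 | 8.3 | 55% | 24.7% |

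The last column uses 66 against 198 infants, a two-sided 5% test and the normal approximation with pooled variance under the null. The nominal value in that direction is 2.5%. Nothing comparable was computed for survival.

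**The case against.** **The shared criteria already remove many unstable infants.** Every group requires "having spontaneous breathing after birth" and excludes intubation before surfactant, major anomalies and severe birth complications. Many infants too unstable for 60 s of DCC would therefore be excluded from the ICC groups too. This stands and narrows the gap. It does not close it, because none of these criteria screens controls for a prenatal contraindication or for tolerating 60 s.

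**Adjustment is planned.** The logistic model can take in collected proxies such as gestational age, birth weight, maternal complications, Apgar score and cord blood gas. To the extent that selection acts through these, adjustment helps, so it would be wrong to say it can do nothing. Its limits are that, in the stated model, a proxy enters only if it differs between groups at P < 0.1; DCC eligibility is not a listed data item; no DCC+MISA infant is ineligible, so there is no overlap on that variable; and completing 60 s is a post-birth event.

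**Stronger readings that the documents do not support.** A reader might infer:
- that the DCC+MISA group is certainly healthier. That is the expected direction, but the article lists no contraindications and gives no risks for the infants left out.
- that the same-criteria statement is plainly false. It is true of the listed criteria; the problem lies in the group definitions added to them.
- that dropping failed MISA biases the main contrast. The article does not say that infants switched to intubation leave the MISA groups, and the MISA wording is the same in both.
- that the 222 historical infants are picked without a rule. A condensed article may leave that to the full protocol.
- that ICC+MISA is itself depleted of DCC-suitable infants, because the Discussion dates the gradual start of DCC to 2023. The Abstract and Background give 2025, so this cannot be settled from the text.

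**Conclusion.** The concern holds as an asymmetry in group entry. One group has two filters, prenatal eligibility and completed treatment, that the others lack, and relying on common criteria to make the groups alike is therefore not fully justified. The plan could favour DCC+MISA, and the limitations do not say so.

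The size cannot be determined from the documents. Under the assumptions shown, the spurious fall in BPD is 1.4 to 8.3 points, or 9% to 55% of the planned 15-point effect. The low end would matter little; the high end would account for more than half of the planned effect. These figures ignore the logistic model and rest entirely on the assumed share and risk ratio. The shared criteria make smaller values of either more plausible than the group definitions alone would suggest.

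**What to change.** 1. Apply the prenatal DCC-contraindication screen used for the prospective group to both ICC groups, from obstetric records.
2. Define the prospective group by planned cord management at birth. Keep infants with incomplete DCC who otherwise meet the same NRDS, surfactant-route and timing conditions as ICC+MISA. Report completed 60 s DCC as a secondary per-protocol set. The surfactant conditions must stay in place; dropping them from the prospective group alone would create a new asymmetry.
3. Add a sensitivity analysis of all infants meeting the listed inclusion and exclusion criteria, by period, with the same rule in every period.
4. Name the residual selection as a limitation.

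For items 2 and 3, the quality indicator "The rate of DCC among all preterm infants with a gestational age of 23–29 + 6 weeks admitted to the NICU" should help to find the infants concerned. It promises only a rate, however, so contraindication status, the reason for early clamping and outcomes must be added to data collection for infants now in no group.

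The cost is an amended group definition, a chart check, some dilution of the DCC effect by incomplete DCC, and possibly fewer historical controls. If as many as 40% of the 198 controls were lost and not replaced (198 × 0.6 = 119), the standard error of the BPD difference at the planned rates would rise from √(0.1204/66 + 0.2059/198) = 5.4 points to √(0.1204/66 + 0.2059/119) = 6.0 points, because the smaller prospective group contributes most of the variance.

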## Abstract

**Background:**

Preventing early invasive mechanical ventilation (IMV) in preterm infants is critical for reducing bronchopulmonary dysplasia (BPD) and improving outcomes. While delayed cord clamping (DCC) enhances cardiopulmonary stability and minimally invasive surfactant administration (MISA) reduces IMV dependence, evidence on their combined efficacy in extremely preterm infants (<30 weeks gestation) with neonatal respiratory distress syndrome (NRDS) remains limited. We hypothesize that integrating DCC with MISA will synergistically reduce BPD incidence compared to immediate cord clamping (ICC) with either MISA or tracheal intubation-based surfactant delivery.

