#### Exclusion criteria

① Premature infants who have received tracheal intubation prior to the use of PS due to resuscitation or other reasons shortly after birth;② Premature infants with identified or confirmed congenital abnormalities (such as fetal edema, chylothorax, or neuromuscular disease) or severe birth complications (including hemorrhagic shock, air leakage, or early-onset sepsis) that impact respiratory function;③ Newborns who discontinue treatment or have incomplete information;④ Newborns involved in other intervention research studies.

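### Entry to the groups depends on events after cord clamping that DCC may alter, so shared criteria do not by themselves make the DCC and ICC groups comparable

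*Protocol article*

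**What the plan says.** All references are to the protocol article.

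- **Exposure.** In the ICC+MISA group, "Umbilical cord clamping is performed within 20 s after birth"; the ICC+tracheal intubation group has the same limit. In the DCC+MISA group clamping is delayed to 60 s.
- **Conditions for entry.** The inclusion criteria ask for infants "having spontaneous breathing after birth" and for NRDS, where "NRDS is defined as progressive dyspnea that occurs after birth". The DCC+MISA definition puts this step after DCC: "followed by a diagnosis of NRDS". The exclusion criteria remove infants with "tracheal intubation prior to the use of PS due to resuscitation or other reasons shortly after birth". Every group definition also requires that surfactant was given, within 2 h for both MISA groups and within 12 h for the intubation group.
- **Conditions for the DCC+MISA group only.** The infant has no contraindication on prenatal assessment, and the 60 s of DCC was completed.
- **Safeguards offered.** The Participants section states that the criteria are the same for all infants. The Discussion presents this as reducing differences between groups and strengthening validity. The Statistical analysis section adds a logistic model with baseline variables that differ at P < 0.1.
- **Rationale.** The Background says that DCC eases the transition at birth. The Discussion says that "DCC facilitates a smoother transition until premature infants can establish effective pulmonary ventilation and circulation".

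**The concern.** A criterion protects comparability when the exposure cannot influence whether it is met. Here at least three criteria are settled after cord management, and the protocol argues that cord management acts on early breathing and circulation. If so, some infants who would have been intubated at once under ICC, and so excluded, may enter under DCC. Others who would have needed surfactant under ICC may not need it under DCC, and so do not enter. The one-sided requirement of completed DCC probably works in another direction, by favouring stable infants.

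The stake is the main comparison of BPD and survival between DCC+MISA and each ICC group. The Conclusion would apply the result to infants born before 30 weeks in general, whereas the data describe those who passed a filter that may differ by group. The comparison of the two ICC groups with each other is not affected by this mechanism.

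**Working it through.** **1. The plan's own figure.** Inputs from Sample size calculation: p1 = 0.29 (ICC+MISA), p2 = 0.14 (DCC+MISA), k = 3, z values 1.96 and 0.84.

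n2 = (1.96 + 0.84)² × [0.29 × 0.71/3 + 0.14 × 0.86] / 0.15² = 7.84 × 0.18903 / 0.0225 = 65.87, so 66, and n1 = 3 × 66 = 198. With 10% loss, 66/0.9 = 73.3, so 74, and 3 × 74 = 222. The stated sizes reproduce. The concern does not turn on them; they only set the scale below.

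**2. Order of events.**

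| Condition | When settled | Could DCC act on it? |
|---|---|---|
| Spontaneous breathing | After birth; timing relative to clamping not stated | Open |
| No intubation before surfactant | After birth, up to surfactant | Yes, by the protocol's rationale |
| NRDS diagnosis | After birth; explicitly after DCC in the DCC+MISA group | Yes, by the same rationale |
| Surfactant given | Within 2 h or 12 h | Yes, by the same rationale |
| No contraindication to DCC | Before birth | No, but it applies to one group only |
| DCC completed | At 60 s | Part of the exposure; one group only |

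The argument rests on rows two to four and does not need row one.

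**3. Size, by illustration.** Suppose DCC has no effect on BPD and infants eligible under ICC+MISA have the planned rate of 29%. Let a share f of the DCC+MISA group be infants who would not have qualified under ICC, with BPD risk r. Both f and r are assumptions. The 70% used as the upper value of r is the rate in the 20 intubated infants of the centre's earlier study; it is not a measured risk for these infants.

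Apparent DCC+MISA rate = 0.29(1 − f) + f·r

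| f | r = 10% | r = 70% |
|---|---|---|
| 10% | 0.261 + 0.010 = 27.1% | 0.261 + 0.070 = 33.1% |
| 20% | 0.232 + 0.020 = 25.2% | 0.232 + 0.140 = 37.2% |
| 30% | 0.203 + 0.030 = 23.3% | 0.203 + 0.210 = 41.3% |

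At f = 20% the spurious difference is −3.8 or +8.2 points. With 66 against 198 infants and an unpooled two-sided test at 0.05, the chance of a significant result from selection alone is about 9% or 23%. At f = 30% it is about 15% or 43%.

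Infants who leave act in the same way. If a share h of those otherwise eligible, with risk r, drops out of the DCC group, the remaining rate is (0.29 − h·r)/(1 − h). With h = 10%: (0.29 − 0.01)/0.90 = 31.1% if r = 10%, and (0.29 − 0.07)/0.90 = 24.4% if r = 70%. The first resembles infants who no longer need surfactant; the second resembles unstable infants who do not complete DCC.

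**4. The planned adjustment.** The logistic model uses baseline variables of infants already included. It has no information on those removed in each period, so it cannot undo the selection.

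**The case against.** **The population belongs to the question.** The study evaluates DCC with MISA in NRDS, and an infant already intubated cannot receive MISA under non-invasive support. This stands as a reason to keep the main cohort. It does not make the cohort comparable across cord strategies.

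**Timing.** A reader might infer that every entry condition is judged after clamping. The documents do not support that. No time is given for judging spontaneous breathing, and Quality control says that newborns are assessed quickly during delivery, so it may be judged before or during the 60 s.

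**Fact or inference.** A reader might also infer that DCC did change who was eligible. No result in the article shows this. It follows only as a possibility from the stated rationale.

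**Early ventilation.** The Abstract states that "Preventing early invasive mechanical ventilation (IMV) in preterm infants is critical", and it is tempting to say that the design removes any effect of DCC on it. Only intubation before surfactant is excluded. Duration of IMV is a secondary outcome, and need for ventilation during the stay is collected, so later ventilation remains visible.

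**Direction.** It is tempting to say that the design hides a real benefit. That is one possibility. The requirement of completed DCC can push the other way.

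**Article format.** Supportive analyses and exclusion counts may be in a fuller document, and the flow chart is not visible. Their absence is not the point. The point is that the article fixes these group definitions and presents shared criteria as a protection, which they cannot fully be here.

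**Conclusion.** The concern holds in this form: entry depends on events after cord management that DCC may influence, so identical criteria and baseline adjustment do not secure comparability of DCC+MISA with either ICC group. A second, one-sided filter comes from the DCC+MISA definition itself.

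Neither size nor direction can be taken from the documents. Under the assumptions above, with one infant in five differing in eligibility and no true effect, the apparent rate lies between 25.2% and 37.2% against 29%. The planned difference is 15 points, so the shift could matter without being decisive. The finding does not show that the groups do differ. It shows that the stated safeguards cannot rule this out, and that the limitations in the Discussion, which name calendar years, treatment approaches and clinician variation, leave it out.

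**What to change.** 1. Keep the main cohort as defined.
2. Add a supportive comparison by birth period of all inborn infants of 23–29+6 weeks without a major congenital abnormality, whatever their intubation, NRDS, surfactant or completed-DCC status. Outcomes: death or BPD at 36 weeks, and delivery-room intubation.
3. Show it also with the ICC+MISA period restricted to births before DCC began. The Discussion dates gradual introduction to 2023, inside the 2021–2024 period, while the Background says 2025; these statements must be reconciled first.
4. Report by period the numbers removed for no spontaneous breathing, for intubation before surfactant, for no NRDS or no surfactant, and for DCC contraindicated or not completed.
5. Remove the Discussion statement that shared criteria reduce group differences and enhance validity, and name selection after exposure among the limitations.
6. Limit the Conclusion to spontaneously breathing infants with NRDS who received surfactant after the cord strategy was completed, unless the supportive analysis agrees.

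**Cost.** Extra chart abstraction is needed. The quality improvement indicators already use all NICU admissions of this gestation as denominator, but they cover procedure rates only, so outcomes, exclusion reasons and delivery-room deaths must be added. The contrast in the supportive analysis is diluted, because not every infant in a period received that period's regimen. Confounding by calendar time remains. If 2023 is right, the restriction in item 3 leaves two of the four ICC+MISA years.
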